#### Participant timeline:

Figure 2 depicts the participant timeline. Baseline, week 4, week 8, month 3, month 4, month 6 and month 12 visits coincide with routine clinic visits. As part of the clinical trial, there is an extra visit at week 2 where the intervention will be delivered to those randomized to the intervention and both arms will undergo sputum collection.

##### Sample size

The effectiveness of the HATHI intervention will be assessed at 6 months using PEth as the primary outcome. A total sample size of 450 participants provides 80% power at a 5% significance level to detect a minimum mean difference of 90 ng/mL between randomized arms. This calculation assumes a mean PEth of 212 ng/mL (SD = 205 ng/mL), as observed in the ongoing HATHI study. Calculations assume a 10% loss to follow-up, and intra-class correlation coefficient of 0.04 to account for site-counsellor clustering.

#### Recruitment

Participants will be recruited from the HIV and TB clinics at BJGMC and DYPMC and through referrals from peripheral TB & HIV clinics. We will recruit through provider referral. The study team will approach providers in the respective TB and HIV clinics at BJGMC and DYPMC and will request that they refer individuals who endorse alcohol use on the standard National Tuberculosis Elimination Programme patient intake form or ART treatment card. Additionally, study staff will review NTEP registers bi-weekly to identify all potentially eligible participants within 30 days of their TB treatment at BJGMC and DYPMC TB clinics. For eligible participants who decline, reasons will be documented and discussed by study staff. Accrual reports will be reviewed regularly, and additional strategies will be implemented if required to achieve the target sample size. The study team will review HIV registers monthly to identify potential participants. All individuals with HIV and/or TB will then be screened by study staff using the AUDIT-C. Those with AUDIT-C scores ≥ 3/4 (women or transgender individuals/men) will be referred by study staff to the study counselor for consent and eligibility determination.

All recruitment activities will take place in a private room to maintain the confidentiality and privacy of the study participants.

##### Randomization procedures: Sequence generation and allocation concealment

Eligible participants will be randomized in a 1:1 ratio upon completion of the baseline evaluation. The study biostatistician, independent of the trial will generate the randomization sequence in permuted blocks with block size 4, and randomization will be stratified by the presence of TB only; HIV only; and TB/HIV co-infection. Allocation will be concealed using sequentially numbered, opaque, sealed envelopes. The study counselor will enroll and assign participants to the interventions

By nature of the interventions being tested, this will be an open-label trial in which neither the subjects, study coordinators, nor interventionists will be blinded to treatment assignment after randomization. However, to decrease potential sources of bias, research assistants, staff abstracting medical records, and data analysts will all be blinded to treatment arm of individual patients.

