### Intervention

Individuals randomized to the intervention will receive UC plus the HATHI intervention. The **HATHI intervention** is a manualized behavioral intervention that integrates evidence-based components of CBT/MET for alcohol reduction. The content intervention was, systematically adapted for delivery within Indian TB and HIV clinical settings and provides a counselor script to aid consistency and quality of counselor delivery. The intervention comprises four core sessions of approximately 45 minutes each, supplemented by three booster sessions of 10–15 minutes, delivered over a three-month period (at month 3, 4 and 6) and aligned to regular treatment visits when possible. The number of boosters was selected to take advantage of monthly scheduled visit during the 6 months of TB therapy.

HATHI is designed to provide relevant alcohol and health information, enhance motivation, strengthen self-efficacy, and teach practical skills to reduce at-risk alcohol use. Sessions are delivered in a **Motivational Interviewing–informed style**, emphasizing collaboration and client autonomy while encouraging individuals to explore their own reasons for change within a supportive, nonjudgmental context. Table 1 describes session timetable and content.

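### A single disclosed block size of 4, with the counselor role both judging eligibility and assigning in an open-label trial, leaves up to a third of allocations deducible

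*Protocol article*

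**What the plan says.** The section Randomization procedures: Sequence generation and allocation concealment states that "Eligible participants will be randomized in a 1:1 ratio upon completion of the baseline evaluation". The biostatistician, who is said to stand outside the trial, "will generate the randomization sequence in permuted blocks with block size 4". No other block size is given. For the strata, the same section specifies that "randomization will be stratified by the presence of TB only; HIV only; and TB/HIV co-infection"; site is not among them. On concealment: "Allocation will be concealed using sequentially numbered, opaque, sealed envelopes". On who does it: "The study counselor will enroll and assign participants to the interventions". On blinding: "this will be an open-label trial in which neither the subjects, study coordinators, nor interventionists will be blinded to treatment assignment after randomization".

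Under Recruitment, people who screen positive on the AUDIT-C "will be referred by study staff to the study counselor for consent and eligibility determination". Informed Consent Procedure also has study counselors take consent. The Intervention section describes a manual that "provides a counselor script to aid consistency and quality of counselor delivery", and Table 1 places session 1 on the day of enrollment. Trial Design calls the trial on-going, so the block size became public while the trial was running.

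**The concern.** Permuted blocks conceal the next assignment only if the people who enroll cannot work out where they are in a block. Here the block length is fixed and public, past assignments are known to interventionists, and the same role title covers eligibility, consent, assignment and delivery. Envelopes protect the card, not the inference from earlier cards.

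A counselor who can foresee the next arm has some room to act on it. Eligibility Criteria contains an exclusion that needs judgement (inability to take part in sessions because of illness severity, cognitive dysfunction or psychosis). The timing of consent can also vary, since TB participants may enter at any point within 30 days of starting therapy. If such choices tracked the expected arm, the arms would differ at entry in ways that randomization should prevent.

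The primary analysis under Aim 1 is a univariable regression on arm with random effects for site and counselor, so it would carry such a difference into the result. Adjusted models are supportive only, and the covariates they list as examples do not include baseline PEth.

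**Working it through.** The plan gives no figure for predictability, so there is none to reproduce. The inputs from the plan are block size 4, 1:1 allocation (two per arm in each block), three disease strata, two sites (Study setting) and a total of 450 (Sample size).

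**1. Observer who sees every earlier allocation in the stratum.** The six equally likely orders are AABB, ABAB, ABBA, BAAB, BABA and BBAA, which make 6 × 4 = 24 positions. In AABB and BBAA, positions 3 and 4 are both fixed by what came before. In the other four orders only position 4 is fixed.

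- Certain: (2 × 2 + 4 × 1) / 24 = 8/24 = 33.3%.
- In 450 complete-block allocations: 450 / 3 = 150.
- Best-guess success, always guessing the arm with more places left: position 1 gives 1/2; position 2 gives 2/3; position 3 gives (1/3) × 1 + (2/3) × (1/2) = 2/3; position 4 gives 1. The average is (1/2 + 2/3 + 2/3 + 1) / 4 = 70.8%, against 50% by chance.

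**2. Observer who sees only part of a shared sequence.** The article does not say how envelopes are divided between the two sites. Suppose one sequence per stratum is shared and the observer handles each allocation independently with probability p, knowing from the envelope number where blocks begin. Position 3 is certain if positions 1 and 2 were both seen and match: p² × 1/3. Position 4 is certain if both earlier allocations to the opposite arm were seen: p². The certain share of the observer's own allocations is therefore (p²/3 + p²) / 4 = p²/3.

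| Share of sequence seen (assumed) | Certain | Best-guess success (simulated below 100%) |
|---|---|---|
| 100% | 33.3% | 70.8% |
| 75% | 0.5625/3 = about 19% | about 65% |
| 50% | 0.25/3 = about 8% | about 60% |
| 25% | 0.0625/3 = about 2% | about 55% |

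**3. Effect of changing the block size, for an observer with full history.** The fixed sizes are exact enumerations. The varying sizes are from 1,500 simulated sequences of 150 allocations (150 per stratum is an assumption), with an observer who knows the set of sizes but not the current one.

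| Block scheme | Certain | Best-guess success |
|---|---|---|
| Fixed 4 (plan) | 33.3% | 70.8% |
| Fixed 6 | 25.0% | 68.3% |
| Fixed 8 | 20.0% | 66.6% |
| Random 4, 6 | about 5% | about 69% |
| Random 4, 6, 8 | about 2% | about 68% |

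Varying the size removes nearly all certain knowledge but little of the guessing advantage, so it is not a complete remedy by itself.

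**The case against.** A fixed block of 4, with an independently generated sequence and sealed opaque envelopes, is a recognized choice and contradicts nothing else in the document. Most entry criteria are objective: AUDIT cut-offs, age, microbiology, HIV status and the treatment window. Higher-risk drinkers need clearance from psychiatry faculty. Study staff search the TB registers bi-weekly and the HIV registers monthly, and screen with the AUDIT-C before the counselor sees anyone. Reasons for declining are documented. Research staff blinded to assignment do the baseline assessment, and randomization follows it. PEth is a laboratory assay, and nothing suggests that its result is available when eligibility is judged. Baseline characteristics will be summarized by arm, with sensitivity analyses if they are imbalanced.

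All of this stands, and it narrows the scope for steering enrollment. It does not prevent deduction within a block. Blinded assessors and an objective outcome protect measurement, not the choice of who enters or when.

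Two stronger readings are not supported. A reader might take one third as the predictable share in this trial. It is an upper bound that needs sight of the whole stratum history, and with two sites and an unstated division of envelopes the true share could be far lower. A reader might also infer that one person judges eligibility, assigns and treats. That rests only on a shared role title, and the fidelity section implies that there are several counselors.

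**Conclusion.** The concern holds as a design weakness that can be cheaply improved, not as an error. Up to one third of allocations can be deduced with certainty, with a best-guess success of about 71%. These figures assume complete blocks, a known block size and full sight of the stratum's earlier allocations. With partial sight of a shared sequence the certain share is about 19%, 8% or 2%.

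The document shows a risk of selection bias and gives no evidence that it has happened. A reader might want to express the risk as a bias in ng/mL and compare it with the 90 ng/mL target difference. That would need the proportion of predictions acted on and the resulting shift in mean PEth. The document gives neither, so no such figure is justified.

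**What to change.** Whether recruitment is still open is not stated, and allocations already made cannot be changed. If it is open:

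1. Have the independent biostatistician issue the remaining allocations, within the existing disease strata, in randomly varying block sizes (for example 4, 6 and 8) that are not disclosed to site staff or published before enrollment ends.
2. Because guessing remains possible, have eligibility confirmed and recorded before the envelope is opened by existing staff who do not see allocations, such as the blinded research staff. Handing only the envelope-opening to the study coordinators would not be enough: they too are unblinded, and a counselor who judges eligibility would still know past arms.
3. Record the date of the change, and compare baseline PEth and AUDIT by arm before and after it. The planned baseline summary by arm covers part of this; the split by date is new.

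If recruitment has closed, a comparison of baseline PEth and AUDIT by arm and by position in block is still informative.

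The cost is a new set of envelopes, a change to who records eligibility, and slightly larger possible arm imbalance within a stratum.

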#### Data Collection and Management

##### Data collection for Aim 1 and Aim 2

###### Research Data Ascertainment:

Research staff blinded to treatment assignment will complete assessments at baseline (prior to randomization), week 2, 4 and 8, and months 3 (end of 4 session intervention), 4, 6, and 12 post-baseline. Data collection visits will be coordinated with scheduled TB or HIV clinic visits. Data collection will include self-report questionnaires (entered on tablets), staff interviews, and biomarker and specimen collection. We include this breadth of measurement strategies to increase the accuracy and scope of our findings (Table 3).

###### Assessment Instrument Selection:

We will use validated instruments to obtain information on alcohol and drug use, mood and quality of life and medication adherence. The baseline research interview is expected to take approximately 1.5 hours. Follow-up data collection will take about 1 hour. Since assessment alone can modify behavior, instruments were selected to balance the need for study data across several outcome domains with the time constraints of data collection. Alcohol measures: Alcohol outcomes, will be measured by a direct alcohol biomarker PEth, a dried blood spot used from the blood sample drawn for other tests. Additionally, drinking days, heavy drinking days, and drinks per drinking day will be measured using the TLFB.

###### PEth:

This direct metabolite of alcohol consumption is formed only in the presence of alcohol, thus it is uniquely specific for recent drinking.(42).(64) PEth is measured in dried blood spots using liquid chromatography with tandem mass spectrometry. The limit of qualification is 8 ng/mL. A value above 50 ng/mL is frequently used to indicate heavy drinking.(64)

###### TLFB:

Using structured interview prompts, the TLFB quantifies alcohol use on each day over the last 30 days. TLFB yields detailed quantity/frequency data including number of abstinent days and drinking days, mean number of drinks/drinking day, and number of heavy (binge) drinking days.(44)

###### Other alcohol measures:

Other measures collected and indicated on Table 3 include measures of alcohol use severity and consequences: MINI International Neuropsychiatric Interview for DSM5)(38); Alcohol Use Disorders Identification Test (AUDIT);(46) the alcohol abstinence self-efficacy scale and an alcohol craving scale.(51, 52, 65)

###### TB Measures:

TB outcomes of medication and appointment adherence will be measured using self-report, biomarkers and clinic records. We use the AIDS Clinical Trial Group (ACTG) adherence questionnaire to measure adherence. In addition, urine and blood samples will be collected to measure urine Isoniazid metabolites and TB drug levels respectively. Retention in care will be measured through clinic registration records and through study records. Sputum will be obtained to determine time to sputum conversion. TB treatment outcomes of cure, treatment failure, and recurrence will be abstracted from the TB treatment card.

###### HIV Measures:

HIV outcomes of medication and appointment adherence and viral suppression will be measured via self-report, clinic registration records, and HIV-RNA measurement, respectively. We will use a self-report 30-day antiretroviral adherence using a visual analog scale,(60) ACTG 4-item adherence questionnaire(61) and pharmacy refill records. Retention in care will be measured through clinic registration records. HIV-RNA and CD4 cell count: HIV-RNA will be drawn as part of the study (as this is not routinely done); CD4 cell count will be abstracted from medical records and drawn if not available.

###### Blood collection:

Blood samples will be collected at baseline, week 4 or 8, 3 months, 6 months and 12 months. The participants will be asked to fast overnight before the blood collection. The blood samples will be used to measure Complete Blood Count (CBC), liver function test, and storage of plasma samples at −80°C for biorepository and future biomarker assessments.

###### Urine samples:

As a secondary measure of TB treatment adherence, we will also measure Isoniazid (INH) metabolites in urine as an objective marker. For people with TB with or without HIV, urine samples will be collected at four time points – baseline, 4 or 8 weeks, 3 months and 6 months. They will be used in a point-of-care test called IsoScreen (GFC Diagnostics) using manufacturer’s directions. This 5-minute dipstick test will assess for TB treatment adherence by measuring INH metabolites in urine. This reflects INH use in the prior 24 hours.

###### TB drug levels:

As a secondary measure of TB treatment outcome, we will also store plasma samples at −80°C for future assessment of TB drug levels (K2 EDTA plasma for Rifampicin and sodium heparin plasma for INH and ethambutol) to study how they are impacted by the intervention. For TB with or without HIV participants, at week 4 or 8 and month 3, blood samples will be collected for pharmacokinetics, 2-hour post TB treatment dose to measure TB drugs.

###### Stool sample:

For participants with TB with or without HIV, stool samples will be collected at four timepoints – baseline, 4 or 8 weeks, 3 months and six months for future assessments on the impact of the intervention on the gut microbiome, and to study the potential mediating role of gut microbiome in the relationship between alcohol use and adverse TB treatment outcomes to complement the parent aims of the study. A pea size scoop of stool size will be self-collected by study participants at home using a kit (NAP-G) with stabilizing transport medium and then will be aliquoted and stored at the study site lab at −80°C until future use. Sample storage: A biorepository will be created to store the plasma and stool samples for future assessments on the impact of the intervention on the microbiome, metabolome and other biomarkers and the potential mediating role of these biomarkers in the relationship between alcohol use and adverse TB treatment outcomes to complement the parent aims of the study. While blood investigations for PK and biomarkers and stool for gut microbiome are important, participants can refuse the collection of samples for ancillary studies and still take part in the main study.

###### Data collection for Aim 3

Following the RE-AIM framework, we will collect qualitative and quantitative data (Table 4) which includes the Mental Health Implementation Science Tool developed for low and middle-income settings. These include assessment of implementation outcomes reach, adoption, feasibility, acceptability, and appropriateness.(66). In addition to these measures on implementation outcomes, we will also include a mixed methods assessment of implementation predictors based on the Consolidated Framework for Implementation Research (CFIR),(67) which will include quantitative items and probes for interviewers to use during qualitative interviews and focus groups.

### Costing measures:

data for economic evaluation will be collected in parallel to the trial to estimate the incremental costs and cost-effectiveness of the HATHI intervention package compared to usual care. Figure 3 provides complete summary of the data collected for the economic evaluation.

#### Time and motion studies:

Data on direct clinical and research staff time committed for implementing and delivering the HATHI intervention will be collected as units of key distinctive service – predefined to distinguish research versus programmatic activities – for each individual participant enrolled in our study from enrolment until end of the follow-up. Time data will be used to assess clinical staff per-patient workloads (i.e. human resource needs to deliver the HATHI intervention) and as an apportionment criterion for fixed costs (e.g. capital assets, overheads) and common costs (resources that are used across more than one distinctive activity in delivering the intervention) in activity-based costing.

#### Health system and implementation costs:

Data on health systems costs will be collected from the perspective of India’s National TB Elimination Program, which is the institution primarily responsible for financing the TB control program. Implementation cost data will be collected using a standardized activity-based time and resource use form following the framework developed by our team(48) and interviews of our research staff, which will be matched to the periodic expenditure log. HATHI intervention costs (other than human resource – assessed using time and motion data and clinical staff pay scales) and other medical service costs (e.g., clinic visit, diagnostics, drugs, etc.) will be collected based on per-patient, service-use frequencies.

#### Patient costs:

Patient’s direct out-of-pocket and indirect costs will be assessed using a modified WHO Patient Cost Survey designed to additionally assess costs associated with alcohol use behavior changes during the study follow-up as well as the patient costs for TB care. Direct costs include costs of medical service fees, transport costs, care-giver costs, and other relevant out-of-pocket costs incurred by patients during intervention participation and TB treatment. Indirect costs account for lost productivity due to alcohol use behavior as well as TB illness, financial coping strategies (e.g., borrowing, selling personal commodities, etc.). As part of this survey, we will also collect patients’ self-reported annual personal and household income and measures of socio-economic status to calculate modified Kuppuswamy scale.(68)

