##### Economic evaluation (Specific Aim 4)

For economic evaluation, we will assess three types of costs: implementation process costs, per-patient service delivery costs, and patient perspective costs. Implementation cost will be defined as cumulative total programmatic cost of the HATHI intervention implementation, categorically analyzed by three phases of implementation: design, initiation, and maintenance phase.(48) HATHI intervention delivery cost will be assessed as per-patient cost, incorporating implementation costs and direct healthcare resources utilized. Patient perspective costs will be assessed as cumulative patient direct out-of-pocket and indirect costs during the participants’ TB treatment until the end of patient follow-up. For cost-effectiveness analysis, the primary outcome will be the incremental cost per alcohol-free patient at endline. Secondary outcomes include incremental cost per improvements in health-related quality of life (HRQoL) score measured using the WHO QoL-BREF(49) and/or EQ-5D.(50) Additionally, we will use the trials’ primary and secondary clinical effectiveness outcomes to estimate modeled long-term projections of health-related quality of life improvements attributable to alcohol reduction and TB treatment outcomes assessed in terms of disability adjusted life years (DALYs) averted.

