#### Aim 4: Cost and cost-effectiveness analysis

Cost of the HATHI intervention will be assessed using activity-based costing framework and ingredients approach where resource use and cost data will be assessed based on key HATHI intervention activities. Fixed costs (e.g., HATHI implementation costs) and resources common across multiple intervention activities will be apportion to each activity based on the distribution of direct human resource time committed to each intervention activities. All costs will be assessed in both local (Indian Rupees) and study year United States (US) dollars, with capital assets and fixed costs annuitized using 3% discount rate (varied between 0 and 10% in sensitivity analyses) and relevant expected useful life years.

For patient cost analysis, we will assess the number and percentage of patients avoiding catastrophic cost due to TB as a result of the intervention relative to the control arm. Catastrophic cost will be defined as TB-related patient-incurred cumulative total costs during the observational period exceeding 20% of patients’ annual household income.(71) We will examine the association between catastrophic costs and AE (e.g., treatment failure) using univariable and multivariable analyses generating odds ratios for each variable as risk factor to the catastrophic costs. This will be assessed independently for each study arm and repeated as a combined analysis for difference in proportion of participants experiencing catastrophic costs between the two study arms.

Cost-effectiveness of the intervention will be assessed based on ‘net benefits’ or net-monetary benefits approach,(72) where we will calculate incremental health systems costs per one additional patient successfully completing TB treatment and bench mark this metric against a range of willingness to pay thresholds, starting with the India’s GPD per capital for our analytic year. We will conduct additional analyses on key effectiveness outcomes – incremental cost per participant achieving alcohol reduction and per quality adjusted life years gained – to examine the relationships in the cost-effectiveness outcomes and conclusions across different effectiveness measures.

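### Borrowing and asset sales are classed as indirect costs; if loan principal or sale proceeds are entered, patient costs are counted twice and the effective 20% catastrophic-cost cut-off falls

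*Protocol article*

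**What the plan says.** Three places in the protocol article together define the patient-cost result.

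- **Patient costs.** The direct component is described thus: "Direct costs include costs of medical service fees, transport costs, care-giver costs, and other relevant out-of-pocket costs incurred by patients during intervention participation"; the sentence goes on to include TB treatment. The indirect component is described thus: "Indirect costs account for lost productivity due to alcohol use behavior as well as TB illness, financial coping strategies (e.g., borrowing, selling personal commodities, etc". Borrowing and selling possessions therefore stand beside lost productivity as contents of indirect cost.
- **Economic evaluation (Specific Aim 4).** The total is direct plus indirect: "Patient perspective costs will be assessed as cumulative patient direct out-of-pocket and indirect costs during the participants’ TB treatment until the end of patient follow-up".
- **Aim 4: Cost and cost-effectiveness analysis.** The endpoint is a threshold on a total: "Catastrophic cost will be defined as TB-related patient-incurred cumulative total costs during the observational period exceeding 20% of patients’ annual household income". It is used to contrast the arms: "we will assess the number and percentage of patients avoiding catastrophic cost due to TB as a result of the intervention relative to the control". The same classification is the outcome in models that give odds ratios for risk factors.

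None of these places says that coping is only described, that loans and sales are netted against the costs they pay for, or that only interest or a loss on sale is counted.

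**The concern.** Borrowing and selling possessions do not use up resources in the way that fees, transport or lost wages do. They show where the money came from. A participant who borrows to pay a clinic fee bears the fee; the loan principal is not a second cost. If the fee enters as out-of-pocket cost and the loan enters as indirect cost, the total holds the same money twice.

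This matters because the endpoint is a yes/no classification at a fixed line. Adding financing amounts can push a participant over that line but can never pull one back. Two results would be affected: the proportion with catastrophic cost, and the total cost from the patient's side.

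**Working it through.** **Inputs.** The only fixed figure in the document is the 20% threshold (Aim 4: Cost and cost-effectiveness analysis). It states no expected catastrophic-cost rate, cost distribution or frequency of borrowing, so there is no figure of the plan's own to reproduce. The financed share is an assumption, shown over a range.

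**Notation.** Let c = (TB-related out-of-pocket cost + TB-related lost income) / annual household income. Let f = the share of that cost paid for by borrowing or sales.

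**Step 1: the two totals.** Without financing amounts the total is c. With principal or proceeds added it is c + f·c = c(1+f).

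**Step 2: effective cut-off.** c(1+f) > 20% holds when c > 20%/(1+f). A participant is wrongly called catastrophic when 20%/(1+f) < c ≤ 20%.

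| f | Effective cut-off on true cost | Band misclassified |
|---|---|---|
| 0.10 | 20%/1.10 = 18.2% | 18.2% to 20% |
| 0.25 | 20%/1.25 = 16.0% | 16.0% to 20% |
| 0.50 | 20%/1.50 = 13.3% | 13.3% to 20% |
| 0.75 | 20%/1.75 = 11.4% | 11.4% to 20% |
| 1.00 | 20%/2.00 = 10.0% | 10.0% to 20% |

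**Step 3: one record (assumed figures).** Income is 100,000 rupees, TB-related out-of-pocket cost 9,000 and TB-related lost income 7,000. True cost is 16,000/100,000 = 16%, not catastrophic. A loan of 6,000 paid part of this, so f = 6,000/16,000 = 0.375 and the effective cut-off is 20%/1.375 = 14.5%. Adding the loan gives 22,000/100,000 = 22%, catastrophic.

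**Step 4: illustration of the proportion.** This step rests wholly on assumptions. Take true cost share as lognormal with median 10% of income and log-SD 0.8 (simulated, one million draws).

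| Who finances, and how much | Catastrophic proportion |
|---|---|
| No financing amounts added | 19.3% |
| 25% of participants finance half their cost | 23.5% |
| 50% finance half | 27.6% |
| 50% finance all | 34.7% |

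Under the same three financing patterns, with medians of 5%, 10% and 15% and log-SDs of 0.8 and 1.0, the excess runs from 1.7 points (4.1% to 5.8%) to 16.7 points (36.0% to 52.7%). The width of that range shows that the document does not determine a size.

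**The case against.** **The sentence describes data collection and gives no formula.** This is partly right. It falls under costing measures, is loosely built, and does not say what amount is entered for coping. Interest paid, or a loss on a forced sale, would be a genuine extra cost. The finding is therefore conditional on principal or proceeds being entered. But the text is not merely silent: it assigns borrowing and selling to indirect cost, and another section adds indirect cost into the total.

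**The detail may lie elsewhere.** Figure 3 and the modified survey could not be consulted for this point, and an article condenses its full protocol. They may show that coping is handled separately. If so, the published classification still needs a correcting line, because as it stands it points the other way.

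**Alcohol-related losses.** A reader might infer that lost productivity from drinking also enters the 20% test, so that the intervention could lower catastrophic cost due to TB simply by reducing drinking. The document does not support this. The endpoint counts TB-related costs only; alcohol-related losses are collected for the wider patient-cost picture.

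**Arm comparison.** A reader might also infer that the contrast between arms is biased. Nothing in the document shows this. It gives no reason to expect borrowing to differ by arm, and no cost data from which to work out how the difference would move.

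**Conclusion.** The point holds in conditional form. If loan principal or sale proceeds are entered as the classification implies, costs are counted twice and the effective cut-off falls to 20%/(1+f). That follows from the plan's own threshold and needs no distributional assumption; only f is unknown. The direction is certain: the catastrophic-cost proportion and total patient cost can be overstated but not understated. The number of participants misclassified cannot be derived, and the simulated proportions are illustrations, not estimates.

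The reach is limited to a secondary Aim 4 patient-cost result. The PEth primary outcome and the sample size are untouched, as is the net-benefit analysis, which uses health-system costs. The correction is still worth making, because it is specific and nearly free.

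**What to change.** 1. In Patient costs, take coping strategies out of indirect costs and report them as a separate hardship indicator (for example, the proportion who borrowed or sold possessions, by arm).
2. In Aim 4: Cost and cost-effectiveness analysis, state that the numerator of the 20% rule is TB-related out-of-pocket cost plus TB-related lost income. Interest or loss on a sale may be added if wanted; principal and proceeds may not.
3. Apply the same rule to total patient cost.

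The cost is a few lines of wording and the matching analysis code. Provided the survey records borrowing and sales as separate items, no new data are needed. The trial is ongoing, so the change can be made before analysis. If financing amounts would otherwise have been added, the reported catastrophic-cost proportion will be the same or lower.
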